### Sample size calculations

The primary endpoint is the incidence of POD in the first 5 postoperative days. Based on the unpublished retrospective observational study enrolled 49 patients in Beijing Friendship Hospital, Capital Medical University, China, the incidence of POD in elderly patients undergoing elective laparoscopic radical colectomy was 35.7%, while it was 14.3% in the other elective laparoscopic surgery. We hypothesize that short-term inhalation of xenon during anesthesia can reduce the incidence of POD down to the same level as patients in the other elective laparoscopic surgery. To achieve a power of 80% with a two-tailed alpha of 0.05, 61 patients are at least needed in each group. Considering 8% potential dropouts or losses to follow-up, we will enroll 66 patients in each group, leading to a total sample size of 132 patients.

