### Study outcomes

#### Primary outcome: Incidence of POD as assessed by 3-Minute Diagnostic Interview for Confusion Assessment Method (3D-CAM)

The primary endpoint of this study is the incidence of POD during the first 5 days after surgery. The assessment will be conducted daily using a Chinese version of 3D-CAM by a blinded investigator during face-to-face follow-up. The Chinese version of 3D-CAM has been demonstrated to have high sensitivity (82.6–93.8%) and specificity (96.7–98.1%), along with strong reliability and validity [27]. A positive result on the Chinese version of 3D-CAM is based on the presence of four criteria: (1) acute onset and fluctuating course; (2) inattention; (3) altered levels of consciousness; and (4) disorganized thinking. POD is defined if both criteria 1 and 2 are present, with at least one of criteria 3 and 4.

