#### Secondary outcomes

Severity of POD assessed with Delirium Rating Scale-Revised-98 (DRS-R-98).

The severity of POD will be assessed daily using the Chinese version of DRS-R-98. This scale is composed of 13 items, and the total score ranges from 0 to 39 points [28]. The severity of POD for each patient will be determined based on the highest value recorded on the scale during the first 5 postoperative days.

(2)Duration of POD assessed by 3D-CAM.

Duration of POD will be measured in terms of the number of days from the onset of delirium symptoms to the resolution of these symptoms.

(3)Subtype of POD assessed with the Richmond Agitation and Sedation Scale (RASS).

The subtype of POD will be defined based on the RASS score as follows [29]: hyperactive type, RASS score > 0; hypoactive type, RASS score < 0; mixed type, the hyperactive and hypoactive types occur alternately.

(4)Postoperative pain level during rest and physical activity measured with a 0–10 point VAS.

Postoperative pain level during rest and physical activity will be evaluated daily using the VAS [30]. Furthermore, the dosages of all opioids for postoperative pain control will be recorded and converted to morphine milligram equivalents.

(5)Sleep disturbance assessed with PQSI.

Patients with POD often experience pre- and postoperative sleep disturbances [31]. Therefore, PSQI scores will be determined at baseline and during the first 5 postoperative days. A sleep disorder will be defined if the PSQI score is higher than 5.

(6)Intraoperative relevant parameters.

Various intraoperative parameters, including blood loss, fluid volume, hypotension (defined as mean arterial pressure (MAP) below 65 mm Hg), hypertension [defined as systolic blood pressure (SBP) and/or diastolic blood pressure (DBP) greater than 30% of their baseline values, or SBP is ≥ 140 mmHg and/or (DBP) is ≥ 90 mmHg, tachycardia (defined as heart rate > 100 bpm), bradycardia (defined as heart rate < 50 bpm), arrhythmia and operation time will be recorded.

(7)Postoperative non-delirium complications and economic parameters.

The postoperative non-delirium complications, such as postoperative nausea and vomiting, pulmonary infection, myocardial infarction, and renal failure, will be documented. Economic parameters, including hospital stays, total hospital costs, and anesthesia-related expenditures, will also be recorded.

(8)Tissue/blood sampling and laboratory parameters.

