### Statistical analysis

Statistical analysis will be conducted using SPSS 23.0 software by qualified statisticians from the clinical research center of Beijing Friendship Hospital. Due to the need for repeated evaluations of patients during the trial process, which may affect patient compliance, we will analyze the outcomes using both the Full Analysis Set (FAS) and the Per-Protocol Set (PPS) and compare the results from both analyses. The FAS will include all participants who are randomized according to the intention-to-treat principle, regardless of whether they strictly adhered to the trial protocol. Missing values in the FAS will be processed using the Last Observation Carried Forward (LOCF) method. The PPS will be defined as the population who strictly followed the trial protocol. This dual approach ensures a comprehensive assessment of xenon’s effectiveness, considering both generalizability and protocol adherence.

All statistical tests will be 2-sided, and a *p* value < 0.05 will be considered to indicate statistical significance. The choice of statistical tests will depend on the types and distributions of the parametric data.

The primary outcome, incidence of POD within the first postoperative 5 days, will be analyzed using *χ*^*2*^ tests.Categorical secondary outcomes, including subtypes of POD; the rates of intraoperative hypotension, hypertension, tachycardia, bradycardia, and arrhythmia; postoperative sleep disorder; and non-delirium complications, will also be analyzed with the* χ*^*2*^ test.Parametric data will also be tested for homogeneity of variance by using the Levene median test. If the data follow a normal distribution and exhibit homogeneity of variance, they will be expressed as mean ± standard deviation and compared between groups using the *t*-test. When data do not meet the criteria for normal distribution or have uneven variances, they will be presented as median (interquartile range) and compared between groups using the Mann–Whitney *U* test.The within-group comparisons of data at multiple time points will be performed with the repeated-measures ANOVA.Time-to-event outcomes, such as the duration of POD and hospital stay, will be analyzed using the log-rank test.The logistic regression analysis will be utilized to examine the factors influencing the primary outcome between groups while controlling for covariates, such as preoperative frailty score, postoperative pain, and pre- and postoperative sleep disturbances.

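### Duration of POD, as defined and tested, exists only for patients who become delirious, so its log-rank comparison is not randomised and may be biased in either direction

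*Protocol article*

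**What the plan says.** Secondary outcomes, item 2, measures the duration of POD with the 3D-CAM as "the number of days from the onset of delirium symptoms to the resolution of these symptoms". The Statistical analysis section then classes it as a time-to-event outcome and fixes the test: "Time-to-event outcomes, such as the duration of POD and hospital stay, will be analyzed using the log-rank test".

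Two general rules in the same section bear on the point. On the analysis set: "The FAS will include all participants who are randomized according to the intention-to-treat principle". On missing data: "Missing values in the FAS will be processed using the Last Observation Carried Forward (LOCF) method". Neither gives a duration for a patient who has no delirium.

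The Sample size calculations section plans for POD incidences of 35.7% without xenon and 14.3% with it, and for 66 patients per arm. POD is assessed daily over the first 5 postoperative days.

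**The concern.** A time from onset to resolution needs an onset. Put together, the definition and the log-rank test leave a comparison of delirious control patients with delirious xenon patients. Randomisation balances the full arms. It does not balance subgroups picked out afterwards by an event that the treatment is expected to prevent.

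If xenon works as hypothesised, the xenon cases are the patients whom xenon could not protect, while the control cases also include those whom it would have protected. Any difference in natural episode length between these two kinds of patient then appears as a treatment effect on duration. At stake is the reading of a named secondary outcome: a trial could show that xenon prevents POD and, from the same data, seem to show that it prolongs POD or that it shortens it, when it does neither to any individual episode.

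**Working it through.** **Inputs from the protocol.** Incidences 0.357 and 0.143; 61 evaluable and 66 enrolled per arm; two-sided alpha 0.05; power 80%; 5-day daily assessment. The protocol states no episode durations, so every duration below is an assumption.

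**1. The protocol's own figure.** Two-proportion formula with unpooled variance: (1.96 + 0.8416)² × (0.357 × 0.643 + 0.143 × 0.857) / 0.214² = 60.35, rounded up to 61. This matches, so the two rates are used as the protocol intends them.

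**2. Who has a duration.**
- At 66 per arm: 66 × 0.357 = 23.6 control and 66 × 0.143 = 9.4 xenon, 33 of 132 in all.
- At 61 per arm: 21.8 and 8.7, or 30.5 of 122.

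**3. What the log-rank test could detect.** With 33 resolutions split 71:29, the hazard ratio detectable with 80% power is exp(2.80 / √(33 × 0.714 × 0.286)) = 2.94. With 30 resolutions it is about 3.1. Power for a hazard ratio of 2 is about 40–44%.

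**4. One constructed data set.** Control: 14 one-day and 10 three-day cases. Xenon: 9 three-day cases.
- Cases only: means 44/24 = 1.83 and 27/9 = 3.00 days. Log-rank: on day 1, 14 of 33 resolve, and the expected number in xenon is 14 × 9/33 = 3.82. On day 3 everyone left resolves (expected 9, no variance). Observed minus expected = 9 − 12.82 = −3.82; variance = 14 × (9/33) × (24/33) × (19/32) = 1.65; z = −2.97, p = 0.003 against xenon.
- All 66 per arm, zeros included: 44/66 = 0.67 and 27/66 = 0.41 days; Mann–Whitney p = 0.0095 in favour of xenon.
- Incidence, 24/66 v 9/66: uncorrected χ² p = 0.003 in favour of xenon.

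This example is extreme. With control unchanged and 1, 2, 3 or 5 of the 9 xenon cases lasting one day, the log-rank p becomes 0.017, 0.069, 0.21 or 0.89.

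**5. Range of assumed durations.** Simulation with 66 per arm and up to 3,000 runs per row. In each arm 14.3% are delirious whatever the treatment, 21.4% only without xenon, and 64.3% never. Durations are capped at 5 days.

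| Mean days, prevented / unpreventable episodes | Log-rank points against xenon | Significant against | Significant for | Mean POD days, all patients, control v xenon |
|---|---|---|---|---|
| 2 / 2 | 49% | 3% | 3% | 0.71 v 0.29 |
| 1.5 / 3 | 94% | 33% | 0% | 0.74 v 0.42 |
| 1.2 / 3 | 97% | 42% | 0% | 0.68 v 0.42 |
| 1.5 / 3, xenon shortens the rest by 10% | 87% | 18% | 0.3% | 0.74 v 0.38 |
| 1.5 / 3, xenon shortens the rest by 20% | 70% | 7% | 0.6% | 0.74 v 0.34 |
| 3 / 1.5 | 1% | 0% | 53% | 0.83 v 0.22 |

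Only in the two shortening rows does xenon alter the length of any episode. In the last row, the 53% is a spurious shortening.

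**6. Check on the remedy.** A rank test over all patients, with about 64% and 86% zeros, largely repeats the incidence test. If all 24 control and 9 xenon cases last exactly 2 days, it gives p = 0.003. If control cases last 1 day and xenon cases 5 days, mean days are 24/66 = 0.36 v 45/66 = 0.68, worse on xenon, yet the rank test gives p = 0.02 in favour of xenon. The mean difference is therefore needed as well.

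**The case against.** **The restriction is inferred.** No sentence says that duration is tested in POD cases only, the FAS is all randomised patients, and an unseen analysis plan might assign 0 days to the rest. This limits certainty about what will actually be run. It does not rescue the text: the protocol fixes both the definition and the test, LOCF cannot carry forward a value that was never defined, and scoring 0 days would replace the onset-to-resolution definition, which is the change asked for here.

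**The durations are invented.** They are, and the example in step 4 loses significance once two xenon episodes are short. A reader might infer that the planned test will count against xenon whenever xenon works. The protocol does not support that: it says nothing about which episodes xenon would prevent, and the bias reverses if they are the long ones. The selection itself needs no assumption about duration.

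**Subtype.** A reader might also infer that the χ² test on POD subtypes has the same fault. The Statistical analysis section sets no POD-only denominator and lists subtypes among whole-arm rates, so a comparison over all randomised patients fits the wording. The subtype scheme ("hyperactive type, RASS score > 0; hypoactive type, RASS score < 0", plus mixed) does leave out a delirious patient with RASS 0. That is a separate matter of category definition with no shown effect on a result, and is not part of this point.

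**It is one unpowered secondary outcome.** True. Low power is to be expected there and is not itself the fault.

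**Conclusion.** The point holds for duration of POD alone. As defined and tested, the comparison covers about 24 control and 9 xenon patients out of 132, selected by the outcome under study. It is not a randomised comparison, and the direction of its bias cannot be known in advance. Over the assumed durations, the test pointed against xenon in 1% to 97% of runs, with significant results against it in up to 42% and spurious significant shortening in up to 53%.

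The case counts rest on the protocol's planned incidences; the percentages rest on durations assumed for illustration. The primary χ² comparison and the sample size are untouched. Hospital stay, named in the same log-rank sentence, is defined for every patient and does not share the fault. The change is worth making before analysis, but it does not threaten the trial's main conclusion.

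**What to change.** - Make the between-group duration outcome the number of POD-positive days in postoperative days 1–5 for every FAS patient, with 0 for those never delirious.
- Report the difference in mean POD days with a confidence interval, for example by bootstrap or permutation, alongside any rank test.
- State that this measures total delirium burden and overlaps with the primary outcome, because a rank test with many zeros largely re-tests incidence.
- Report onset-to-resolution time among POD cases descriptively, without a between-group p value.
- Remove duration of POD from the log-rank sentence.

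**Cost.** Wording only. The daily 3D-CAM assessments already supply the data, and 30 participants had been recruited when the article was written. The downside is that the comparison no longer isolates episode length. The mean difference will also be imprecise. In the step 4 example it is 0.41 − 0.67 = −0.26 days. The sample variances are 1.15 (control) and 1.08 (xenon), so the standard error is √((1.15 + 1.08)/66) = 0.18 and the 95% interval is about −0.62 to 0.10.

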### Blinding and randomization

The eligible patients will be randomized to either the control group or the xenon group using a computer-generated randomization sequence. Randomization will be performed in a 1:1 ratio, and allocation will be concealed using sealed envelopes. Both the study subjects and investigators assessing outcomes will be blinded to group assignments, and the study statisticians will perform the data analysis after the trial is completed.

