To mitigate these disparities, several improvements have been in the protocol. Firstly, the heterogeneity among study subjects is a critical factor contributing to inconsistent research conclusions. For instance, while a randomized clinical trial in patients undergoing elective off-pump coronary artery bypass graft surgery demonstrated a significant reduction in POD incidence with 50–60% xenon anesthesia [34], similar benefits were not observed in studies involving on-pump cardiac surgery [35] or hip fracture surgery [36]. Variations in patient age, surgical types, and comorbidities contribute to these discrepancies. In order to avoid these confounding factors, we focus on elderly patients undergoing laparoscopic radical colectomy, a high-risk and extremely vulnerable patient group for POD [6–9]. And patients with surgery durations exceeding 6 h and those planned for postoperative ICU admission are excluded to minimize variability in surgical procedures and reduce selection bias. Secondly, practical considerations during trial implementation have been carefully taken into account. For example, administering multiple questionnaires over five consecutive days postoperatively may lead to patient fatigue and non-compliance. Therefore, outcomes will be analyzed using both FAS and PPS, providing comprehensive and robust results to better understand xenon's potential protective effects. This approach enhances the reliability of the trial and aids in identifying and addressing potential biases and data variability. And the logistic regression analysis will be utilized to examine the high-risk factors influencing the primary outcome between groups, such as preoperative frailty score, postoperative pain, and pre- and postoperative sleep disturbances. Moreover, considering the high cost of xenon is a significant barrier to its clinical research and widespread adoption, xenon will be administered only for a short time, that is, 1 h after anesthesia induction, a period associated with a higher likelihood of hemodynamic instability [37–39].

Despite the inability to blind the anesthesiologist due to the use of a closed-circuit xenon delivery system integrated with the anesthesia machine, strict adherence to a standardized hemodynamic treatment protocol will ensure equivalent management in both groups and minimize bias. Additionally, both investigators and study statisticians assessing primary and secondary outcomes will be blinded to group assignments.

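### The supporting logistic regression of delirium adjusts for postoperative pain and sleep, which arise after xenon is given, so its xenon odds ratio may not estimate the total xenon effect

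*Protocol article*

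**What the plan says.** The Statistical analysis section of the protocol article assigns the primary outcome, POD in the first five postoperative days, to a χ² test. The last item of the same section adds a logistic regression that looks at influences on POD between the groups while "controlling for covariates, such as preoperative frailty score, postoperative pain, and pre- and postoperative sleep disturbances". The Discussion repeats the list ("such as preoperative frailty score, postoperative pain, and pre- and postoperative sleep disturbances").

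Two of the four named variables, frailty and preoperative sleep, are baseline measurements. The other two are not:

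- **Pain** is item 4 of the Secondary outcomes: "Postoperative pain level during rest and physical activity will be evaluated daily using the VAS".
- **Sleep** is item 5, scored with the PSQI at baseline and over the first five postoperative days. The protocol motivates it by noting that "Patients with POD often experience pre- and postoperative sleep disturbances".

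Under Interventions, xenon is given during anesthesia, shortly after induction. Both postoperative variables therefore follow treatment.

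**The concern.** A randomised comparison is protected because nothing measured before treatment can differ systematically between arms. Adjusting for a variable measured after treatment gives up that protection in two situations.

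1. **Xenon changes the variable.** If the variable also influences POD, holding it fixed removes the part of the xenon effect that runs through it. If it only shares an unmeasured cause with POD, adjustment creates an association that randomisation had excluded.
2. **POD changes the variable.** Postoperative PSQI is scored in the window in which POD is assessed, and nothing requires the covariate to precede the delirium. Adjusting for a consequence of the outcome distorts the comparison.

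The plan treats both variables as things xenon might change, since it compares them between arms as outcomes, and then holds them constant when it examines POD. This regression is the only adjusted model described for the primary outcome, so readers will set it beside the χ² result. A weaker or reversed odds ratio could be mistaken for evidence about xenon when it reflects only the choice of covariates.

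**Working it through.** **Inputs from the Sample size calculations and Blinding and randomization sections.** POD "was 35.7%, while it was 14.3% in the other elective laparoscopic surgery", the second figure being the level assumed under xenon. "To achieve a power of 80% with a two-tailed alpha of 0.05, 61 patients are at least needed in each group". An allowance of 8% for dropout brings this to 66 per arm, with equal allocation.

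**The plan's own figure.** With unpooled variance:

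n = (1.960 + 0.842)² × (0.357 × 0.643 + 0.143 × 0.857) / 0.214² = 7.849 × 0.3521 / 0.0458 = 60.35, rounded up to 61.

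61 × 1.08 = 65.9, rounded up to 66. Both stated figures are reproduced. The calculation is a two-proportion one with no covariates, so this point does not touch it.

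**Planned effect.** OR = (0.143/0.857) / (0.357/0.643) = 0.30. Risk difference (RD) = 14.3 − 35.7 = −21.4 points.

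**Illustration.** The documents give no effect of xenon on pain or sleep, and no effect of either on POD, so the following values are assumptions. M is one continuous post-treatment covariate with residual SD 1. As a mediator, it has a log-odds ratio of b = 0.7 per unit for POD. Each scenario simulated 400,000 patients with the overall POD rates held at 35.7% v 14.3%, except in the last row. A logistic model with arm and M was then fitted. The RD is that model's prediction averaged over M.

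| Assumed structure | Adjusted OR | RD (points) |
|---|---|---|
| M predicts POD; xenon does not change M | 0.27 | −21.4 |
| Mediator, xenon lowers M by 0.3 | 0.33 | −18.1 |
| Mediator, lowered by 0.5 | 0.39 | −15.5 |
| Mediator, lowered by 0.8 | 0.47 | −12.4 |
| M and POD share an unmeasured cause; xenon lowers M by 0.5 | 0.34 | −18.6 |
| POD raises M by 1; xenon does not otherwise change M | 0.30 | −17.8 |
| POD raises M by 1; xenon also lowers M by 0.5 | 0.50 | −10.3 |
| No total effect (25% v 25%); mediator lowered by 0.5 | 1.42 | +6.0 |

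**Hand check of the mediator rows.** M has the same spread in both arms, so a shift a in its mean moves a × b out of the arm coefficient: ln OR(adjusted) = ln OR(a = 0) − a × b. With OR(a = 0) = 0.272, ln = −1.302:

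- a = −0.3: −1.302 + 0.21 = −1.092, OR 0.34 (simulated 0.33)
- a = −0.5: −1.302 + 0.35 = −0.952, OR 0.39
- a = −0.8: −1.302 + 0.56 = −0.742, OR 0.48 (simulated 0.47)
- no total effect, a = −0.5: 0 + 0.35, OR 1.42

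**Reading the table.** In the first row the OR moves from 0.30 to 0.27 only because odds ratios change when any prognostic covariate is added. The RD does not move, so there is no bias. In the sixth row the OR happens to survive at 0.30, but the RD shrinks. In every row where xenon lowers M, the adjusted OR lies above 0.27, or above 1 when there is no total effect.

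**Expected events.** 66 × 0.357 + 66 × 0.143 = 23.6 + 9.4 = 33.

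**The case against.** The strongest reply has four parts.

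1. **The primary analysis is an unadjusted χ² test, and the sample size was calculated for it.** This stands. A reader might infer that the primary result is biased or that the trial loses power. The documents do not support that, because the regression is a supporting model on which no power was claimed.

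2. **The regression is risk-factor exploration.** The Discussion presents these variables as high-risk factors for POD, and neither section promises an adjusted xenon odds ratio. This stands in part. The Statistical analysis section nevertheless describes a between-group examination with these variables as controls. Neither place labels the model as prognostic or mediational, or leaves treatment out of it. An adjusted group effect is therefore a fair reading.

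3. **Bias is not shown.** The Background attributes the hoped-for benefit to NMDA antagonism, hemodynamic stability and anti-inflammatory action, not to pain or sleep. Both arms receive the same analgesic regimen with the same pain target, which may narrow any difference. The sentence on sleep states an association without a direction. All of this stands, so the stronger statement that the adjusted effect is biased goes beyond the documents. They support only that it can be.

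4. **The covariate list is given as examples.** This disposes of any complaint that age and MMSE are not named. It does not excuse the two postoperative variables that are named.

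A reader might also infer that pain and POD share the same five-day window. The Secondary outcomes section gives that window for PSQI; for pain it says only that assessment is daily.

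**Conclusion.** The point holds for the supporting regression only. As worded, the plan can produce an adjusted xenon odds ratio that does not estimate the total effect of xenon on POD. This happens if xenon changes pain or sleep, or if they partly result from POD. Neither condition is established, but the trial compares both variables as outcomes and itself links sleep disturbance with POD, so it is unsafe to assume that neither applies.

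The size cannot be computed from the documents. Under the assumed mediator effects of 0.3 to 0.8 SD, the planned OR of 0.30 becomes about 0.33 to 0.47. With no total effect, a 0.5 SD reduction gives about 1.4, an apparent harm. If neither condition holds, the RD stays at −21.4 points. These figures show direction and plausible scale; they are not predictions. The point merits a change of wording and does not threaten the primary conclusion.

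**What to change.** In the Statistical analysis section, and to match in the Discussion:

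- State that any adjusted comparison of xenon with control uses only a short prespecified list of baseline covariates already collected, such as frailty score and preoperative PSQI, with age and MMSE as options. About 33 expected events argue for keeping the list short.
- Move postoperative pain and postoperative sleep to a separate analysis labelled as exploratory risk-factor or mediation work, and state that its treatment coefficient is not to be read as the xenon effect. Both remain secondary outcomes.

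The cost is wording only: no new data, no change to the sample size and no change to the primary test. The current text is an approved third version with 30 participants recruited, so the change should be documented. It should be made before the unblinded interim analysis planned at about half of recruitment.
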